## Analyses

Data entry forms were built for each measure in the study to correspond to the paper forms that the assessors used. REDCap (Harris 2012) requires outer limits for each value, and each paper data sheet is double entered for purposes of data verification process. Collectively these features optimize the data entry accuracy. Study data will be kept for seven years following conclusion of the trial, at which point data will be destroyed following REB requirements.

Descriptive statistics and graphic displays will be presented for all outcomes for the PT and Lokomat interventions (pre, post-test and change scores). Equivalence between baseline_A_ and baseline_B_ scores will be evaluated for each outcome; a t-test or Wilcoxon test will be used in this comparison as appropriate. The primary analysis will be for the pre- to post-test differences (change scores) of the GMFM-66 and 6MWT between groups. Assuming normality of data, a repeated measures ANCOVA will be performed on GMFM-66 and 6MWT change scores to compare the effects of the Lokomat and gait-related PT interventions. The child’s relevant baseline score (baseline_A_/baseline_B_) will be used in the ANCOVA to increase analytic precision. The P value will be adjusted to 0.025 to handle the expected high correlation between the GMFM-66 and timed walk. Evaluation of an intervention order effect (i.e., being the first or second treatment), as well as the interactions with intervention group will be built into this analysis (Senn 2002). Secondary sub-analyses will be done in the same way within GMFCS II and III subgroups to determine any differential response for GMFCS Level.

Due to the lack of expectation of return to baseline in the break period, a second analytic approach will be taken as well using a generalized estimating equation (GEE) adjustment for repeated measures within subjects analysis (Baker et al. 2007). In this approach treatment effects are evaluated via regression analysis and the GEE method will allow the fit of two models. The first is for treatment effect, treatment-period effect, and differential carryover effect adjusting for the baseline scores, and the second is treatment effect and treatment-period effect with exclusion of any differential carryover effect. Factors hypothesized a priori to be associated with GMFM-66 change score magnitude will be entered within this model using a forward stepwise regression procedure, e.g., age, GMFCS Level, motivation (DMQ) score, ASK baseline score.

Finally, a third approach will be taken if there is significant evidence of a carryover effect and significant interaction effects. This will be to focus on the data from the first arm of the study, i.e., an ANCOVA adjusted for baseline GMFM-66 change scores of just the first intervention period (randomisation to either Lokomat or PT with 20 children per group). This comparison in itself would have a power of about 0.60 for the GMFM-66 (with alpha = 0.025 and a medium effect size of 0.50).

A similar set of analytic approaches will be used for the secondary outcome measures (GMFM Stand and Walk, Timed Up and Go, walk velocity/step and stride length [from GAITRite], observational gait scale, average daily step counts [step activity monitor data], Quality FM, *Challenge* Assessment, ASK-30, PEDI Part II, KIDSCREEN, COPM and GAS scores), using the baseline value of the measure of interest as a covariate within a MANCOVA procedure that will permit simultaneously handling of multiple secondary outcome measure change score evaluations. If both parent and child filled out the questionnaires (i.e., all children 8 years of age and up who were able to do so), the children’s data will be analysed as primary. Otherwise parent questionnaire data will be considered as primary. A comparison of child and parent questionnaire results will be done as a secondary analysis via an ANOVA in which both single point in time (baseline) and change scores will be evaluated. ROM and Tardieu scores will be summarized in a simpler manner, using descriptive statistics and graphical presentations to illustrate scores in each phase. The power of all primary and secondary ‘no difference’ analyses will be determined post hoc.

The primary analysis will include all children who attended ≥70% of sessions for each intervention, and those who discontinued one or both interventions for a reason directly related to the study (e.g., excessive fatigue associated with participation or issues related to dislike of one or both interventions), or dropped out of the trial due to an intervention-associated injury. In the case of dropout due to study fatigue or dislike of the intervention, a strong effort will be made to do a discharge assessment at the time of withdrawal. In the case of injury, it may be possible to follow the child and evaluate some of the outcomes when the child is able (post-minor injury). If the physical assessment is not possible due to compromised physical status, completion of the functional and participation measures may still be appropriate.

A second analysis will include all who adhered to ≥50% of each intervention as well as those who discontinued one or both interventions for reasons noted in the primary efficacy analysis. The third analysis will be an “intent to treat”, including the last available data from all participants regardless of level of adherence or reason for withdrawal. As outlined above, a strong effort will be made to do a discharge assessment at time of withdrawal. Demographic characteristics, baseline scores and change scores of these three adherence groups will be evaluated to determine any systematic differences in their characteristics or outcomes.

Data from the session summary sheets will be compiled. Treatment categories, Lokomat parameter adjustments, and session activities will be summarized through graphic and tabular summaries, and related descriptive information from therapists’ comments will be reported.

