**Methods/design:**

In this two-group cross-over RCT, children are randomly allocated to the RAGT or PT arm (each with twice weekly sessions for eight weeks), with cross-over to the other intervention arm following a six-week break. Both interventions are grounded in motor learning principles with incorporation of individualized mobility-based goals. Sessions are fully operationalized through manualized, menu-based protocols and post-session documentation to enhance internal and external validity. Assessments occur pre/post each intervention arm (four time points total) by an independent assessor. The co-primary outcomes are gross motor functional ability (Gross Motor Function Measure (GMFM-66) and 6-minute walk test), with secondary outcome measures assessing: (a) individualized goals; (b) gait variables and daily walking amounts; and (c) functional abilities, participation and quality of life. Investigators and statisticians are blinded to study group allocation in the analyses, and assessors are blinded to treatment group. The primary analysis will be the pre- to post-test differences (change scores) of the GMFM-66 and 6MWT between RAGT and PT groups.

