## Study aims and hypothesis

The primary aim of the study is to determine the impact on gait-related gross motor skills of a gait training program using a robotic-assisted gait trainer (the Lokomat^®^Pro) compared with a gait-related physiotherapy (PT) program for children in GMFCS Levels II and III. The primary hypothesis is that children receiving the Lokomat intervention will improve more on the GMFM-66 and 6-minute walk test (6MWT) than those in the gait-related PT program.

The secondary objective is to evaluate the comparative impact of Lokomat training and gait-related PT on: (a) individualized walking/gross motor based goals; (b) the amount/location of walking the child does each day (environmental context and season considered); (c) participation in activities and (d) health-related quality of life.

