## Sample size

The study has been designed and powered to ensure adequate sample size for the primary research questions and analysis of children in GMFCS Levels II and III. The starting point for our sample size calculation consideration was a single group Lokomat study with a similar GMFCS sample and Lokomat use protocol in which the GMFM Stand and Walk mean scores changed by approximately 5 points (SD change = 7) (Borggraefe et al. 2010b). Our study is powered to let us detect a difference between the two interventions of three points (SD = 6: small effect size) on the GMFM-66, a magnitude of change that is considered to be a minimally clinically important difference (Oeffinger et al. 2008) when evaluating benefits of treatment. The reason for a difference change target in our study is that we are comparing two active interventions, each of which could result in positive change given the walking focus and boost for many of the children in therapy intensity. This sample size is also sufficient to handle the 6MWT comparisons and the small effect size observed by others in single group Lokomat studies in the 6MWT results (mean gains of 25 m [SD = 50 m], personal communication, Glenrose Hospital program, 2012).

For crossover designs, sample size calculations that link with a matched pairs *t* test calculation are appropriate (Senn 2002). A paired *t* test is also the underlying basis for the more sensitive repeated measures ANOVA that we have chosen to use so that we can include a period effect within the analysis. With an alpha of 0.025, beta of 0.20, and a detectable change score difference between intervention of thre points on the GMFM-66 (with an estimated SD of change of 6.0 points), a sample of 32 children is required (Hintze 2001). We increased the sample requirement to 40 to account for a potential drop out/protocol deviation rate of 20%. Sample calculation based on this generous drop-out rate will support the primary efficacy analysis that focuses only on the children who attend more than 70% of the sessions within one or the other intervention phase.

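### The 0.025 level on each co-primary outcome is a valid split given a wrong reason (correlation); if it splits an overall two-sided 0.05, Holm gives more power for the second outcome at the same 5% ceiling

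*Protocol article*

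**What the plan says.** The Abstract (Methods/design) names two primary outcomes: "The co-primary outcomes are gross motor functional ability", measured by GMFM-66 and 6MWT. Study aims and hypothesis joins them in one directional sentence: "children receiving the Lokomat intervention will improve more on the GMFM-66 and 6-minute walk test (6MWT"). The article does not say whether one or both must succeed.

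Analyses sets the level for the two tests: "The P value will be adjusted to 0.025 to handle the expected high correlation between the GMFM-66 and timed walk". It gives no overall alpha, no sidedness and no stepwise procedure.

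The same level enters Sample size: "With an alpha of 0.025, beta of 0.20", with a "detectable change score difference between intervention of thre points on the GMFM-66" and "with an estimated SD of change of 6.0 points". This leads to 32 children, raised to 40 for 20% loss. The first-period fallback in Analyses also quotes its power at alpha 0.025.

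**The concern.** Alpha is divided between two tests because there are two chances of a false positive. When the outcomes are highly correlated, the two chances overlap and the problem shrinks. The article therefore gives as its reason the feature that makes the adjustment least necessary.

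The consequence is practical. With the purpose of the adjustment stated correctly, the next question is whether a claim may rest on one outcome or needs both, and each answer has a more efficient standard rule than a fixed 0.025 on both tests. What is at stake is power for the second outcome, in a hypothesis that names both. The validity of the error rate is not at stake.

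**Working it through.** **Inputs.** From Sample size: difference 3 points and SD 6.0 for GMFM-66, a ratio of 0.5; power 0.80; alpha 0.025, sidedness not stated; 32 evaluable, 40 enrolled; a paired calculation ("For crossover designs, sample size calculations that link with a matched pairs" *t* test). For 6MWT the article gives "mean gains of 25 m [SD = 50 m"], also a ratio of 0.5. That is a single-group gain, so its use as a between-intervention effect is an assumption. The correlation is not given, so a range is shown.

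**1. The plan's own figure.** n = ((z_alpha + z_power) × SD / difference)².
- One-sided 0.025 (the same as two-sided 0.05): ((1.960 + 0.842) × 6/3)² = 31.4, so 32. An exact paired *t* calculation gives 34.
- Two-sided 0.025: ((2.241 + 0.842) × 6/3)² = 38.0, so 39. Exact *t* gives 41.
- Loss: 32 / 0.80 = 40.

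The stated 32 matches one-sided 0.025, or two-sided 0.05. It does not match two-sided 0.025.

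**2. Effect of correlation on the split.** With no effect on either outcome and two-sided 0.025 on each test, family-wise error = 1 − P(|Z1| < 2.241 and |Z2| < 2.241). At correlation 0 this is 1 − 0.975² = 0.0494. From the bivariate normal:

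| Correlation | Family-wise error at 0.025 each | Per-test level giving exactly 0.05 |
|---|---|---|
| 0 | 0.0494 | 0.0253 |
| 0.5 | 0.0465 | 0.0270 |
| 0.7 | 0.0430 | 0.0293 |
| 0.9 | 0.0362 | 0.0350 |

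Higher correlation calls for less adjustment.

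**3. The alternatives, if 0.025 is a split of an overall two-sided 0.05.**
- *Either outcome supports its own claim.* Holm tests the smaller p against 0.025 and, if that succeeds, the other against 0.05. It rejects everything the fixed split rejects and sometimes the second outcome too, with family-wise error at most 0.05. Its first step is the fixed split, so error with no effect on either outcome is identical.
- *Both required.* A false overall claim needs rejection of at least one true null, so 0.05 on each keeps the overall error at or below 0.05.

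**4. Power.** Two-sided paired *t* tests, n = 32, standardised effect 0.5 on both outcomes, simulated with 100,000 trials per correlation:

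| Correlation | At least one (fixed and Holm) | Both, fixed 0.025 | Both, Holm | Both, 0.05 each |
|---|---|---|---|---|
| 0.5 | 0.83 | 0.53 | 0.65 | 0.66 |
| 0.7 | 0.80 | 0.56 | 0.67 | 0.69 |
| 0.9 | 0.75 | 0.62 | 0.70 | 0.73 |

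Before rounding, Holm gains about 12 points for both outcomes at correlation 0.5 and about 9 at 0.9. Power per outcome is (at least one + both) / 2:
- Correlation 0.5: (0.83 + 0.53)/2 = 0.68 fixed; (0.83 + 0.65)/2 = 0.74 Holm.
- Correlation 0.9: (0.75 + 0.62)/2 = 0.685 fixed; (0.75 + 0.70)/2 = 0.725 Holm.

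That is 4 to 6 points per outcome.

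**5. What the gain costs.** With effect 0.5 on one outcome and none on the other, the false-claim rate is about 2.5% under the fixed split and about 3.8% to 4.1% under Holm (correlation 0.9 to 0.5). If both are required, it is 1.3% to 1.5% at 0.025 each and 2.6% to 3.4% at 0.05 each.

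**The case against.** The strongest reply is that nothing is broken. Two tests at 0.025 form a Bonferroni split, valid at any correlation, with simple simultaneous confidence intervals. This stands: the fault is one of rationale and efficiency. A reader might infer from a wrong reason that the error rate is inflated. The table in step 2 shows the opposite.

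A reader might also infer that the fixed split buys nothing in error control. That is true only of the nominal 5% ceiling. When one outcome has a true effect and the other has none, the fixed split has the lower actual error (step 5).

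Third, Holm does nothing for the chance of at least one success. This also stands: the gain is confined to the second outcome and is smallest at the high correlation the article expects.

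Fourth, the size rests on a borrowed 6MWT effect, and Sample size itself expects a smaller contrast between two active interventions. It also takes 32 evaluable children. With 40, the chance of confirming both under the fixed split is 0.68 to 0.74. The figures are illustrations under stated assumptions.

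Fifth, sidedness is open. If 0.025 were an unsplit one-sided level and both outcomes were required, it would be the conventional level and nothing would be lost. The word adjusted, tied to the pair of outcomes, favours a split of 0.05 but does not settle it. The correlation rationale is wrong on either reading.

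Finally, the decision rule and stepwise detail may stand in an SAP that is not shown. Their absence here is therefore not the fault. The fault is the fixed level and the reason that the article does state.

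**Conclusion.** The point holds as one of rationale and efficiency. The stated reason for 0.025 is backwards whatever the sidedness. If 0.025 is a split of an overall two-sided 0.05, the fixed rule gives up 4 to 6 points of power per outcome and 9 to 12 points for confirming both, compared with Holm at the same 5% ceiling. This assumes 32 evaluable children, a standardised effect of 0.5 on both outcomes and correlation 0.5 to 0.9. The chance of at least one success is unaffected.

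Two stronger readings are tempting. One is that the hypothesis, because it joins the outcomes with *and*, requires both to succeed. The sentence names two outcomes and sets no decision rule, so that choice belongs to the sponsor. The other is that this rule leaves the trial short of power. Sample size already uses 0.025, and whether 32 is enough at that level depends on the unstated sidedness (step 1), which is a separate question.

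**What to change.** In Analyses, replace the correlation rationale with the real one: the adjustment is made because two primary outcomes are tested. State that 0.025 is a split of an overall 0.05, if that is meant, and whether the tests are one- or two-sided. Then state the decision rule:
- if either outcome supports a claim for that outcome, use Holm (smaller p against 0.025, then the other against 0.05);
- if the primary hypothesis requires both, test each at 0.05.

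Make the alpha in Sample size and in the first-period power statement in Analyses consistent with the chosen rule. At two-sided 0.025 the stated inputs need 39 to 41 evaluable children; at two-sided 0.05 they need 32 to 34.

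The cost is a few sentences and a rechecked sample-size statement, with no new data, and it should be done before unblinding. The statistical price of Holm is less simple simultaneous confidence intervals and an actual false-claim rate of about 4% instead of 2.5% when only one outcome has a true effect, still within 5%.

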## Study sample and recruitment

The study aims to enrol 40 children with CP (ages 5–12 years) as follows: (a) 20 children in GMFCS Level II who have walking limitations but ambulate without a gait device or crutches or canes for most distances; and (b) 20 children in GMFCS Level III who have a greater extent of walking limitation and use walkers or wheelchairs for short to long distances (Russell et al. 2000).

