### Randomisation

Children who meet the eligibility criteria and pass the screening assessment are assigned a study ID number, and then attend their baseline assessment. Following the baseline assessment, the child is allocated to start in either the Lokomat or PT intervention phase via a process of random assignment using a computer generated random numbers system. The assignment scheme was prepared at the start of the study by a non-study RA, using a stratified randomisation process (age and GMFCS level) that employed mixed allocation blocks of 4 and 6 children. By the end of the trial, this system will ensure that the number and age/GMFCS balance of participants who start in the Lokomat and PT intervention groups will be even. Management of the randomisation process by a non-study RA through the entire study allows the study investigators to remain blinded to the scheme, thereby eliminating allocation bias. Participants are informed of the intervention order by the study RA.

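### The planned separate analyses within GMFCS II and III do not themselves test whether the Lokomat–PT difference varies by level, and no treatment-by-GMFCS term is stated

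*Protocol article*

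**What the plan says.** The primary analysis (protocol article, Analyses) is a repeated measures ANCOVA of GMFM-66 and 6MWT change scores comparing the two interventions. On the threshold it says: "The P value will be adjusted to 0.025 to handle the expected high correlation between the GMFM-66 and timed walk". The subgroup sentence follows in the same paragraph: "Secondary sub-analyses will be done in the same way within GMFCS II and III subgroups to determine any differential response for GMFCS Level". It gives both a method (the same analysis, run within each level) and a purpose (an inference about differential response).

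Two other statements might be thought to supply a direct comparison of levels:

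- The same paragraph of Analyses builds interactions with intervention group into the model, but that sentence is about intervention order (first or second treatment). GMFCS level is not mentioned in it.
- The GEE approach in the next paragraph lists GMFCS level among factors thought to be associated with the size of the GMFM-66 change score, to be entered by forward stepwise selection. That is a main effect: children at one level may change more under either therapy.

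Under Study sample and recruitment the target is "20 children in GMFCS Level II who have walking limitations", and 20 in Level III. GMFCS level is also a randomisation stratum.

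**The concern.** Whether the Lokomat–PT difference depends on GMFCS level is a question about the difference between two effects. Two separate tests against zero do not answer it. With 20 or fewer children per level each test has modest power, so one can reach the threshold and the other miss it by chance even when the true effects are identical.

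The Abstract and Discussion say the results should inform the role of robotic gait training in practice. A chance split between levels could therefore be taken as a reason to regard the therapy as suited to one level and not the other. The Analyses section also applies a similar set of approaches to the secondary outcomes, so the same problem may recur there.

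**Working it through.** **Inputs** (protocol article, Sample size unless noted): difference 3 points and SD 6.0, used in a paired *t* test; alpha 0.025, sidedness not stated; power 0.80; 20% loss allowed for; 20 children enrolled per GMFCS level (Study sample and recruitment), so 20 × 0.80 = 16 per level after that loss.

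**Step 1. Reproduce the plan's own figure.** The plan says: "With an alpha of 0.025, beta of 0.20, and a detectable change score difference between intervention of thre points on the GMFM-66" and "with an estimated SD of change of 6.0 points), a sample of 32 children is required". By the paired normal approximation, n = (SD × (z_alpha + z_power) / difference)².

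- z_alpha = 1.960 (one-sided 0.025, the same as two-sided 0.05): 4 × (1.960 + 0.842)² = 31.4, so 32. The *t* version gives 34.
- z_alpha = 2.241 (two-sided 0.025): 4 × (2.241 + 0.842)² = 38.02, so 39. The *t* version gives 41.

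The 32 is reproduced with the first value, and 32 / 0.80 = 40 matches the enrolment target. Because sidedness is not stated, two-sided 0.025 is taken below as an assumption and the alternative is checked in Step 3.

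**Step 2. Power within one level.** Paired *t* test with n children, noncentrality (effect / 6) × √n, n − 1 degrees of freedom, two-sided 0.025. At 3 points the noncentrality is 0.5 × √16 = 2.00 or 0.5 × √20 = 2.24, and power is 0.342 or 0.439.

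**Step 3. Chance that exactly one level is significant when the true effect is the same in both.** The levels contain different children, so the tests are independent and the chance is 2p(1 − p). At 3 points:

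- 16 per level: 2 × 0.342 × 0.658 = 0.450
- 20 per level: 2 × 0.439 × 0.561 = 0.493

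| Common true effect (points) | Power, n = 16 | Exactly one significant, n = 16 | Power, n = 20 | Exactly one significant, n = 20 |
|---|---|---|---|---|
| 0 | 0.025 | 5% | 0.025 | 5% |
| 1 | 0.054 | 10% | 0.063 | 12% |
| 2 | 0.155 | 26% | 0.198 | 32% |
| 3 (design) | 0.342 | 45% | 0.439 | 49% |
| 4 | 0.580 | 49% | 0.706 | 42% |
| 5 | 0.790 | 33% | 0.891 | 19% |

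A simulation of 100,000 trials with a period-adjusted crossover analysis at 3 points also gave 45% and 49%. Reading 0.025 as one-sided gives 50% (n = 16) and 49% (n = 20) at 3 points. The maximum of 2p(1 − p) is 50%, reached at p = 0.5, so the design effect lies close to the worst case.

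**Step 4. The direct test.** Compare the mean within-child difference in Level II with that in Level III: standard error 6 × √(2/n), degrees of freedom 2n − 2, two-sided 0.025. In the same simulation it declared a difference in 2.6% (n = 16) and 2.5% (n = 20) of trials with a common 3-point effect, which is the nominal rate. Its power for a true difference D between levels is:

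| D (points) | n = 16: D / SE | Power | n = 20: D / SE | Power |
|---|---|---|---|---|
| 3 | 3 / 2.121 = 1.41 | 0.19 | 3 / 1.897 = 1.58 | 0.24 |
| 6 | 6 / 2.121 = 2.83 | 0.68 | 6 / 1.897 = 3.16 | 0.79 |

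**The case against.** The strongest defence is that the protocol never says significance will be compared across levels. Running the analysis in the same way within each level yields an estimate and a standard error for each. Since the levels are disjoint, a reader could compute the difference and its interval from those. Exact model terms are also often left to an analysis plan, and none is shown here. GMFCS heterogeneity is in neither the primary hypothesis nor the listed secondary objectives, and the analyses are labelled secondary.

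Much of this stands. A reader might infer that the planned analyses could never reveal a differential response. The documents do not support that, because the information is available and what is missing is a stated comparison. A reader might also infer that nearly half of all trials without differential response would appear to show one. That figure belongs to a common effect near 3 or 4 points and to a reading rule that the protocol does not spell out. The Sample size section itself notes that both interventions are active and could each produce gains, so a smaller difference is plausible, and the rate is then much lower.

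The mismatch remains. The article does not leave this question open: it names a method and says that the method is to determine differential response. The method does not test that, and no other comparison is stated.

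**Conclusion.** The point holds in this limited form: the stated within-level analyses do not test the question they are assigned, and neither the primary model nor the GEE as described contains a treatment-by-GMFCS term. This does not depend on the size of the effect.

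The size of the risk does. It rests on four assumptions: the true effect is the same in both levels, the SD of the within-child difference is 6, alpha is two-sided 0.025, and differential response is read as one level significant and the other not. On those terms the chance of a misleading split runs from about 5% with no treatment effect to 45–49% at the design effect, and can never exceed 50%. The primary comparison of Lokomat with PT is not affected. The change is worth making because it is cheap and the claim at risk concerns which children appear to benefit.

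**What to change.** Add a treatment-by-GMFCS interaction, with the GMFCS main effect, to the whole-sample primary model for GMFM-66 and 6MWT. State that any conclusion about differential response rests on that term and its confidence interval. Give the Level II and Level III estimates from the same model as descriptive results, and label the analysis exploratory. Where the approach is carried to secondary outcomes, apply the same rule.

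The cost is an interaction term and its main effect in the model and a sentence of text, with no new data, children or visits. The downside is low power (Step 4), and the text should say so: a non-significant interaction would not show that the two levels respond alike.

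### In the supportive GEE analysis, forward stepwise selection of pre-hypothesised factors in 32 to 40 children exaggerates the factors it retains; a closed list, entered and reported in full, would not (minor)

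*Protocol article*

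**What the plan says.** The Analyses section of the Protocol article names a repeated measures ANCOVA on change scores as the primary analysis. Because abilities are not expected to return to baseline in the break, "a second analytic approach will be taken as well using a generalized estimating equation (GEE) adjustment". Two GEE models are described. "The first is for treatment effect, treatment-period effect, and differential carryover effect adjusting for the baseline scores"; the second leaves out differential carryover.

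The section then turns to covariates: "Factors hypothesized a priori to be associated with GMFM-66 change score magnitude" "will be entered within this model using a forward stepwise regression procedure", with the examples "e.g., age, GMFCS Level, motivation (DMQ) score, ASK baseline score". The list is illustrative. The Randomisation section gives two of the four examples, age and GMFCS level, as stratification factors.

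On numbers, the Sample size section says "a sample of 32 children is required", and then: "We increased the sample requirement to 40 to account for a potential drop out/protocol deviation rate of 20" per cent.

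**The concern.** A factor justified in advance has no need of a significance test to earn its place. Forward selection nevertheless lets the same small dataset decide which factors stay. The final model then shows only the survivors, with standard errors computed as though that model had been fixed beforehand. Two distortions follow: the retained coefficients are too large on average, and their intervals cover too seldom. Selection could also drop age or GMFCS level, on which the randomisation was stratified.

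What is at stake is limited to the reported association between child characteristics and GMFM-66 change.

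**Working it through.** **1. Number of independent children.** The plan's figure uses a difference of 3, SD 6 and power 0.80 ("With an alpha of 0.025, beta of 0.20"). By the paired normal approximation, n = (SD × (z_α + z_β) / difference)² = (6 × (1.960 + 0.842) / 3)² = 5.604² = 31.4, so 32. Allowing for 20% loss, 32 / (1 − 0.20) = 40. Both figures reproduce, with 1.960 taken as one-sided 0.025 (or two-sided 0.05). Sidedness does not matter here. The named factors are fixed within a child, so two change scores per child do not raise the number of independent units above 32 to 40.

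**2. The bar for entry.** The plan gives no entry threshold, so p<0.05 is assumed. A single factor enters first only if its sample correlation exceeds t / √(t² + n − 2):
- n = 32: 2.042 / √(2.042² + 30) = 0.35
- n = 40: 2.024 / √(2.024² + 38) = 0.31

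A lone factor with a true standardised slope of 0.2 or 0.3 therefore enters first only when its estimate exceeds the truth. With four true slopes of 0.2 and mutual correlation 0.3 there is a second source of error. The first factor to enter also carries the omitted ones, and its expected coefficient is 0.2 × (1 + 3 × 0.3) = 0.38, which is 1.9 times its own slope.

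**3. Simulation, one outcome per child.** Settings: four candidates, pairwise correlation 0.3 (assumed), entry at p<0.05, n = 32 and 40.

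| Setting | Stepwise, retained | Forced entry, all reported | Forced entry, only significant ones |
|---|---|---|---|
| No true factor: chance of at least one | 15–17% | not applicable | 15–17% |
| One true slope 0.2–0.3: mean estimate | 0.42–0.47 | unbiased | 0.44–0.52 |
| One true slope 0.2–0.3: coverage | 85–92% | about 95% | 83–93% |
| Four true slopes of 0.2: coverage | 73–76% | about 95% | 87–89% |

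For a slope of 0.2, the exaggeration is 0.42 / 0.2 = 2.1 at n = 40 and about 2.2 at n = 32. For 0.3, it is 0.47 / 0.3 = 1.6 at n = 32 and about 1.4 at n = 40.

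**4. Simulation, closer to the planned GEE.** Settings: two change scores per child, SD 6, within-child correlation 0.2 to 0.5 (assumed), treatment and period always in the model, robust standard errors. Baseline and carryover terms were not simulated.
- Four true factors of 1.2 points per SD (1.2 / 6 = 0.2): retained effects 1.9 to 2.2 times too large, coverage 73 to 79%.
- Two true factors of 1.8 and 1.2 points (0.3 and 0.2): retained true effects 1.5 to 1.7 times too large. The correct set is found in 7 to 14% of trials, and two replicate trials choose the same set in 22 to 24%. Coverage over everything retained is 69 to 76%, which includes falsely retained factors.
- Forced entry on the same data: coverage 93.5 to 94.5%.
- No true factor: at least one retained in 21 to 23% of trials. This again looks like multiplicity with slightly liberal robust intervals. Per-coefficient error of 5.5 to 6.5%, treated as independent over four tests, gives 1 − 0.945⁴ = 20% to 1 − 0.935⁴ = 24%.

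**5. Treatment contrast.** A factor that is constant within a child cancels from the difference between that child's two change scores. Which factors are selected therefore hardly moves the within-child comparison of Lokomat with PT.

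**The case against.** The best defence is that stepwise selection is not the main culprit. Anyone who fits all four factors and then discusses only the significant ones meets nearly the same exaggeration, as the last column of the table shows, and the same chance of a false factor. That is correct. With one true factor, the gain comes from reporting every coefficient, not from forced entry as such. Stepwise selection is clearly worse in its own right only when several correlated factors matter (73–76% against 87–89%).

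It is also fair that the analysis is supportive, that the entry rule may be set in a document not shown, and that the examples are not a closed list. An entry rule would change the amount of selection bias but not remove it, and the stepwise method itself is stated here.

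A reader might infer more than the article supports:
- **That the model identifies which children respond better to one intervention.** It does not: the factors are main effects on change pooled over both arms. Differential response by GMFCS level is left to the separate subgroup analyses.
- **That these predictors are meant to guide care.** The aims contain no predictor objective, and the Discussion ties clinical sequencing to the order effect.
- **That the procedure is repeated for every secondary outcome.** The sentence concerns GMFM-66 change only.

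**Conclusion.** The point holds as a minor one. On 32 to 40 children, the stepwise step will overstate the factors it retains, by about 1.4 to 2.2 times for true standardised slopes of 0.2 to 0.3. The attached 95% intervals will cover about 85 to 92% with one true factor, and about 75% with four correlated ones. When all factors are entered and all are reported, estimates are unbiased and coverage is close to nominal.

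The sizes rest on assumptions that the article does not settle: entry at p<0.05, four candidates, correlation 0.3, and the slopes themselves. A looser entry rule would exaggerate less and a stricter one more; the direction does not change. The primary ANCOVA has no stepwise step, and neither it nor the treatment contrast is called into question.

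**What to change.** In the Analyses section, delete the stepwise wording and fix a closed list before the data are analysed. The four examples would serve: age, GMFCS level, DMQ score and baseline ASK score, with the stratification factors age and GMFCS level always kept. Enter them together and report every coefficient with its interval, significant or not. Label the results exploratory and describe them as associations with change, not as modifiers of the treatment effect.

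The change is one of wording and needs no new data: age and GMFCS level are known at randomisation, and Table 1 has DMQ and ASK-30 collected at baseline. The statistical price is about four degrees of freedom. With treatment, period, carryover and baseline score already in the fuller model, that makes roughly 4 + 4 = 8 terms besides the intercept on 32 to 40 children. GMFCS level and ASK may overlap with baseline GMFM-66, in which case their coefficients will be imprecise; the wider intervals would show this openly.
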